### Randomization

At T1, patients are randomly assigned (in a 1:1 ratio) to one of the two groups, namely either to receive standard oncological care alone (Control Group: CG) or standard care plus an exercise program (Training Group: TG), which starts at the halfway point through the chemotherapy protocol. During the follow-up period (T3-T6), both groups follow standard oncological care without supervised PA. Furthermore, the level of PA, without guidelines, is assessed by a connected watch.

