### Primary endpoint

The primary endpoint is a reduction in insomnia assessed by an increase in total sleep time (TST).

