## Statistical analyses

### Sample size

To detect a difference of TST of 10% compared to baseline value (considering a TST of 420 min), between the two groups, at T3, a Z-test with a type I error of 5% and a statistical power of 80% will be used. A total of 57 patients including 29 in CG and 28 in TG are required.

Two interim analyses for the efficacy and futility using the Lan-Demets method (O’Brien Fleming boundaries) to estimate the alpha spending function will be performed at 33% and 66% of the information fraction (after enrolment of 19 and 38 evaluable patients). With 10% of non-evaluable patients, 64 patients should be randomized. The primary objective will be done in modified intention-to-treat (miTT): all randomized and evaluable patients for the TST at T0 and T3.

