### Data analysis

Statistical analyses will be performed with SAS v9.4, and R v4.1. All primary statistical analyses will be conducted on the miTT population. A p-value < 0.05 will be considered statistically significant for the primary and secondary endpoints.

Patient characteristics will be described for all demographic and clinical data recorded at inclusion in the overall population, miTT population and according to group. Qualitative variables will be described with absolute numbers and percentages. Continuous variables will be reported using mean, standard deviation (SD), median, quartile 1-quartile 3 (q1-q3), min-max.

The comparison of average total sleep time for primary endpoint will be performed with Z-test. Comparisons for secondary endpoints will be carried out using Student’s t-test, Wilcoxon rank-sum test, analysis of variance (ANOVA), and Kruskall-Wallis test, as appropriate. The association of qualitative variables will be carried out using chi-square or Fisher’s exact tests, as appropriate.

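### The primary Z-test of total sleep time uses no baseline covariate and is less efficient than a baseline-adjusted analysis of data the trial already requires

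*Protocol article*

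**What the plan says.** The Data analysis section of the protocol article fixes the primary test: "The comparison of average total sleep time for primary endpoint will be performed with Z-test". The Sample size section names the same test: "a Z-test with a type I error of 5% and a statistical power of 80% will be used". Neither section mentions a covariate, an ANCOVA or a mixed model.

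The endpoint and the target both refer to baseline. Under Primary endpoint: "The primary endpoint is a reduction in insomnia assessed by an increase in total sleep time (TST". Under Sample size, the target reads: "To detect a difference of TST of 10% compared to baseline value (considering a TST of 420 min), between the two groups, at T3". The Sample size section also restricts the primary population to randomized patients whose TST is evaluable at both T0 and T3.

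The design has "A total of 57 patients including 29 in CG and 28 in TG are required" and "With 10% of non-evaluable patients, 64 patients should be randomized". Two interim analyses for efficacy and futility "will be performed at 33% and 66% of the information fraction (after enrolment of 19 and 38 evaluable patients").

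**The concern.** A patient without a baseline TST is excluded from the primary analysis, so the trial pays for that measurement in data and in patients. The named test makes no stated use of it to reduce variance. In a trial of 57 evaluable patients, with looks at 19 and 38, precision is scarce.

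The article does not say whether the averages compared are T3 values or changes from baseline. A T3 comparison leaves in the error term all variation that baseline would explain. A change score does use baseline, but it forces the slope on baseline to be 1 when the data would usually support a smaller one. ANCOVA estimates the slope and is at least as precise as either. At stake is power for the primary comparison and the width of its confidence interval.

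**Working it through.** **Inputs from the article.** Target difference 10% of 420 min = 42 min; type I error 5%; power 80%; 29 and 28 evaluable patients (Sample size); allocation 1:1 (Randomization).

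**Inputs not in the article, therefore assumed.** Two-sided testing; the SD of TST (back-solved); the baseline-T3 correlation ρ (range 0.2 to 0.7); equal SDs at baseline and T3. Normal approximation throughout.

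**Step 1: the plan's own figures.** Without an SD, 57 cannot be reproduced from stated inputs, so I solved for the SD that yields it:

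SD = 42 / [(1.960 + 0.842) × √(1/29 + 1/28)] = 42 / (2.802 × 0.2649) = 56.6 min.

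The allowance for non-evaluable patients does reproduce: 57 / 0.90 = 63.3, rounded up to 64.

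Two alternatives for the SD: a one-sided 5% test implies 63.8 min. Allowing for the three-look O'Brien-Fleming efficacy boundaries (sample size inflation about 1.013) implies 56.2 min, so the interims hardly alter the figure.

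**Step 2: if the Z-test compares T3 values.** Then 56.6 min is the SD at T3. ANCOVA multiplies the SD by √(1 − ρ²), and

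power = Φ(2.802 / √(1 − ρ²) − 1.960).

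For example, ρ = 0.5: 2.802 / 0.866 = 3.235; Φ(1.275) = 89.9%.

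Unadjusted sample size per arm is 2 × (2.802 × 56.6 / 42)² = 28.5, so 29 per arm, or 58 with equal arms. ANCOVA multiplies 28.5 by (1 − ρ²) before rounding up.

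**Step 3: if the Z-test compares changes from baseline.** Then 56.6 min is the SD of change, and the planned test has 80% power at every ρ. The variance of change is 2(1 − ρ) times the T3 variance, and the ANCOVA residual variance is (1 − ρ²) times it. Their ratio is (1 + ρ)/2, so

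power = Φ(2.802 / √((1 + ρ)/2) − 1.960).

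For example, ρ = 0.3: 2.802 / √0.65 = 3.475; Φ(1.515) = 93.5%.

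| Assumed ρ | Planned Z-test (either reading) | ANCOVA, 56.6 = SD at T3 | Total N for 80%, same case | ANCOVA, 56.6 = SD of change |
|---|---|---|---|---|
| 0.2 | 80% | 81.6% | 56 | 95.1% |
| 0.3 | 80% | 83.6% | 52 | 93.5% |
| 0.5 | 80% | 89.9% | 44 | 89.9% |
| 0.7 | 80% | 97.5% | 30 | 86.0% |

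The N column compares with 58 for the unadjusted test. The gain rises with ρ on the first reading and falls with ρ on the second. ANCOVA is ahead in every row.

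**Step 4: which baseline.** The Sample size section defines evaluability on TST at T0. The Study outcomes section lists an interview, questionnaires and a sleep diary at T0, and places objective sleep parameters at T1, T3 and T6. TST is an output of both polysomnography and actigraphy, and the Primary endpoint section names neither. A diary could give a TST at T0, but by a different instrument. As the text stands, the covariate cannot be identified.

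**The case against.** The strongest reply is that the planned test is valid. Randomization makes the unadjusted comparison unbiased, and it is the test on which the trial was sized. That stands.

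A reader might infer that baseline TST is simply ignored. The documents do not establish this: the endpoint is worded as an increase, the target is set relative to baseline, and both values are required. All of this fits a change score at least as well. The point therefore rests only on what holds under both readings.

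A reader might also infer that chance imbalance threatens the result, since the standard error of the baseline difference is 56.6 × 0.2649 = 15.0 min. That is about a third of 42 min, and only ρ times an imbalance reaches T3: 4.5 min per standard error at ρ = 0.3, 7.5 min at 0.5. This variation is already counted in the test's standard error and in the 80% power.

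A third tempting inference is that a change score has only 66% power at ρ = 0.3. That figure takes 56.6 min as the SD at T3 while testing change. If the trial was sized on change, the SD is that of change and power is 80%.

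Finally, neither the SD nor ρ is in the article. With one night of home polysomnography and about 12 weeks between measurements during chemotherapy, ρ could be low. At 0.2 the gain over a T3 comparison is under two points. That also stands.

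An unseen analysis plan might add a covariate, but the article states the primary test in two places, so it is not a detail left open.

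**Conclusion.** The point holds as one of efficiency. The primary analysis is a two-group Z-test with no baseline covariate, in a population defined by having a baseline TST, and a baseline-adjusted ANCOVA is more efficient however that test is read. Nothing here makes the planned comparison invalid or biased.

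Against 80%, the gain is about 2 to 17 points of power for ρ from 0.2 to 0.7 if the test is on T3 values, and about 14 to 6 points for ρ from 0.3 to 0.7 if it is on change. These figures rest on the back-solved SD, two-sided 5%, equal SDs at the two times and assumed correlations. The direction rests on none of these values beyond ρ being non-zero (T3 reading) or below 1 (change reading with equal SDs). The size does, and it may be small.

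**What to change.** 1. Reconcile the baseline first. State whether baseline TST is taken at T0 or T1, and from which instrument, and make the definition of the modified intention-to-treat set agree with the visit schedule.
2. Make the primary analysis an ANCOVA of T3 TST on arm, with pre-intervention TST from the same instrument as covariate. Report the adjusted difference in minutes with its confidence interval.
3. Use the same model at both interim analyses, so that the boundaries apply to one statistic throughout.
4. For continuous secondary endpoints where a parametric model is suitable, adjust for each measure's own last pre-randomization value. From Study outcomes this appears to be T0 for the ISI, PSQI, ESS and HADS. For fatigue, pain, inflammatory variables and fitness it is T1, provided the assessment precedes allocation. Rank tests can stay where they are the better choice.

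The cost is protocol and analysis plan wording, to be settled before any comparison by arm. It needs no extra patients. It also needs no extra measurements, provided the reconciled baseline is one already scheduled. If ρ is near zero, the price is one residual degree of freedom (57 − 3 = 54 instead of 57 − 2 = 55).

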Moreover, exercise is recommended during treatment with curative intent. Aerobic and resistance exercise has been shown to reduce fatigue, preserve cardiorespiratory fitness and physical functioning, as well as improve quality of life and depression symptoms [14]. Several trials demonstrated that exercise interventions are feasible in early breast cancer patients and have a low risk of severe adverse events [15, 16].

However, few studies have explored the efficacy of an exercise program for cancer-related insomnia among patients undergoing breast cancer treatments. In this regard, we hypothesize that exercise programs can have a beneficial effect on insomnia for breast cancer patients.

We designed the present randomized FATSOMCAN trial, to examine, in non-metastatic early breast cancer patients with an insomnia diagnosis, the effect on sleep quantity of an individualized, intermittent aerobic exercise training regimen (45 min, 3 times a week), comprising both moderate and high intensity exercise, for a period of 3 months. Secondary objectives are to evaluate the effects of this supervised exercise program on other parameters such as sleep disorders, sleepiness, anxiety/depression, core body temperature and salivary melatonin rhythm. Furthermore, fatigue, pain, inflammatory and cardiorespiratory fitness variables, and level of physical activity (PA) are assessed.

We hypothesize that a supervised exercise program will reduce insomnia and improve the quality and quantity of sleep. Exercise will increase cardio-respiratory fitness, with an improvement in inflammatory variables. We suppose that these modifications will be accompanied by a reduction in sleepiness, anxiety/depression, fatigue and pain. Moreover, we hypothesize that patients who participate in the supervised exercise program will maintain these benefits at the three-month follow-up.

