**Fig. 2 Fig2:**
[figure not shown]
Representation of treatment schedule and different times of evaluation and questionnaire completion

At T-1, all potentially eligible patients have a clinical interview according to the DSM-5 to diagnose the presence of insomnia before treatment by chemotherapy. They also complete the study questionnaires [i.e., the Insomnia Severity Index (ISI), the Pittsburgh Sleep Quality Index (PSQI), the Epworth Sleepiness Scale (ESS) and Hospital Anxiety and Depression Scale (HADS)] and a sleep diary for 2 weeks. The interview, questionnaires and sleep diary constitute the baseline values before inclusion. A clinical examination, including medical history, use of analgesics (type, level, dose), lifestyle habits (work, family environment, physical activity, smoking, alcohol), is also carried out.

At T0, one week after completion of the first sequence of the chemotherapy, patients have a clinical interview, complete the questionnaires and sleep diary again. If insomnia is confirmed, patients can then be included.

At T1, at the end of the 3-month exercise intervention (T3) and at 6 months (T6) of the follow up period, objective sleep parameters, salivary melatonin and core body temperature rhythm are evaluated. At T1 and T3, fatigue, pain, inflammatory variables and cardiorespiratory fitness are assessed. At T3, DMS-5 interview, questionnaires and sleep diary are completed again. From T1 to T6, the level of PA is followed (Fig. 2).

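### For secondary endpoints measured repeatedly in the same patients, no paired or repeated-measures method is named, and none of the listed difference tests can by itself show that the benefit lasts to T6

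*Protocol article*

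**What the plan says.** Data analysis names the tests for secondary endpoints: "Student’s t-test, Wilcoxon rank-sum test, analysis of variance (ANOVA), and Kruskall-Wallis test, as appropriate". It sets one threshold for all of them: "A p-value < 0.05 will be considered statistically significant for the primary and secondary endpoints". No method in the section is labelled paired or repeated-measures.

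The Background ends its hypotheses with the expectation that "patients who participate in the supervised exercise program will maintain these benefits at the three-month follow-up". Under Study outcomes, the schedule evaluates at T1, then "at the end of the 3-month exercise intervention (T3) and at 6 months (T6) of the follow up period, objective sleep parameters", together with salivary melatonin and core body temperature rhythm. Each patient therefore supplies three values for these variables. The Discussion counts follow-up of how long the gains last among the study's strengths.

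The planning difference is 10% of a total sleep time (TST) of 420 min, at T3. On the number of patients, the Sample size section says "A total of 57 patients including 29 in CG and 28 in TG are required".

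**The concern.** The hypothesis about follow-up concerns what happens to the same patients between T3 and T6. The named tests do not fit that question well, for two separate reasons.

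- **Pairing.** Rank-sum and Kruskal-Wallis are defined for independent samples. Applied across visits, they leave the between-patient variance in the error term. Their within-patient counterparts, signed-rank and Friedman, are not named. A skewed endpoint measured repeatedly thus has no suitable within-patient test in the list.
- **Direction of proof.** Every listed test has a null hypothesis of no difference. Within the training group, a non-significant T3-T6 result is compatible with full retention, with substantial loss, or with too few patients to tell.

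What is at stake is the durability conclusion and the precision of the repeated secondary endpoints. The primary comparison of TST at T3 is not affected.

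**Working it through.** TST serves as the example because it is the only variable with a planning difference in the article.

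**Inputs from the article.** Full benefit: 0.10 × 420 = 42 min; half of it is 21 min. Training group: 28; control group: 29. Test: "a Z-test with a type I error of 5% and a statistical power of 80% will be used".

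**The plan's own figures.** Allowing for 10% non-evaluable patients, 57 / 0.90 = 63.3, rounded up to 64, which agrees with the article. The 57 cannot be reproduced independently because the article gives no SD, so I solved for the SD:

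SD = 42 / [(1.960 + 0.842) × √(1/29 + 1/28)] = 56.6 min (two-sided 5%).

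A one-sided 5% reading gives 63.8 min. A sample-size inflation of about 2% for the interim analyses (assumed) would lower the two-sided value only to about 56 min.

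**Further assumptions.** T3-T6 correlation ρ of 0.3, 0.5 or 0.7; equal SD at both visits; normal data; all 28 trained patients measured at T6; true loss of 21 min.

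**Paired t-test.** SD of the change = 56.6 × √(2(1 − ρ)), and its standard error is that divided by √28. Power is from the noncentral t with 27 df.

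**Unpaired t-test on the same data.** The test uses a standard error of 56.6 × √(2/28) = 15.1 min, so with a critical t of 2.005 it needs a difference of about 30.3 min. The true standard error is the paired one. The normal approximation for power is P(Z > (30.3 − 21) / true SE). Simulation (200,000 trials per setting) also allows for the estimated variance and gives slightly higher values.

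| | ρ = 0.3 | ρ = 0.5 | ρ = 0.7 |
|---|---|---|---|
| SD of change (min) | 67.0 | 56.6 | 43.8 |
| True SE (min) | 12.7 | 10.7 | 8.3 |
| Unpaired t, approximation | 23% | 19% | 13% |
| Unpaired t, simulation | 24% | 21% | 16% |
| Paired t | 36% | 47% | 69% |
| Unpaired t, rejection rate with no loss | 2.0% | 0.7% | 0.1% |

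Pairing therefore adds about 12, 27 and 53 percentage points.

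**Other SDs.** At 50 min, paired power is 44%, 57% and 79%, and unpaired power (approximation) 30%, 27% and 21%. At 63.8 min, the figures are 30%, 39% and 58%, and 18%, 14% and 8%.

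**What a paired interval could show.** The 95% CI half-width for the T3-T6 change is 2.052 × SE = 26, 22 and 17 min at the three correlations (SD 56.6). At 0.3 and 0.5, an observed change of zero would not exclude a 21-min loss.

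**Comparison of the arms at T6.** If 21 min of benefit remain, SE = 56.6 × √(1/29 + 1/28) = 15.0 min and 21 / 15.0 = 1.40, which gives 28% power (noncentral t, 55 df). This comparison would usually be non-significant and would read as benefit not shown to persist. An unpaired T3-T6 comparison within the training group would also usually be non-significant, but could be taken as benefit kept. The article does not say which contrast answers the hypothesis.

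**The case against.** The strongest reply is that this is a generic list in a condensed article, qualified by a phrase that leaves the choice of test open, and that contrasts and models may be set in a fuller plan not shown. Much of this stands, and it rules out three stronger readings.

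- A reader might infer that only independent-sample tests are planned. The text does not establish that. Student's t-test and ANOVA have paired and repeated-measures forms, and neither is labelled. Only the two rank tests are independent-sample by definition.
- A reader might infer that a non-significant T3-T6 change will be reported as maintained benefit. No section states that rule.
- A reader might infer that the choice of test is why a half loss would go unseen. Sample size matters at least as much: at SD 56.6 min, even the paired test misses a 21-min loss in about 64%, 53% and 31% of trials at the three correlations.

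It is also fair that comparing the arms at T6 is a legitimate way to address durability, and the listed tests are valid for it. The schedule under Study outcomes places fatigue, pain, inflammation and fitness at T1 and T3 only, so the T3-T6 question mainly concerns objective sleep, melatonin and temperature rhythm.

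The reply does not remove the point. The open-ended phrase selects among the named tests; it does not add signed-rank, Friedman or a mixed model. And a paired t-test or repeated-measures ANOVA would still be a test of difference.

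**Conclusion.** The point holds as a low-cost improvement to a stated choice of method. The article names tests for repeatedly measured endpoints without naming any paired or repeated-measures method, two of the four are unsuitable within patients, and none can alone support the maintenance hypothesis. Arm comparisons at T3 or T6 remain valid, but leave the T1 value and the within-patient correlation unused.

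The power loss is conditional: it arises only if an unpaired test is actually used for T3 against T6. It then amounts to 24%, 21% and 16% against 36%, 47% and 69% at correlations 0.3, 0.5 and 0.7. The SD of 56.6 min is back-solved and the correlations are assumed; the article gives neither. The direction of the comparison is the same at 50 and 63.8 min.

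**What to change.** In Data analysis, for continuous secondary endpoints measured repeatedly, replace the list with a linear mixed model for repeated measures. Include arm, visit and arm-by-visit terms and the T1 value, with patient as the correlated unit. Report the arm contrast at each post-randomisation visit at which the endpoint is measured. Name signed-rank or Friedman tests as the fallback for within-patient questions where the model does not fit.

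For durability, state that the conclusion rests on the T6 arm difference with its 95% CI. Report the training group's T3-T6 change with its 95% CI alongside it, and state that p > 0.05 will not be taken as evidence of maintenance. A retention margin fixed before analysis would sharpen this, but is optional.

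The cost is revised wording and a little programming in SAS or R, both already planned; no new patients or measurements are needed. The real price is that maintenance becomes harder to claim: with 28 trained patients, the result may have to be reported as inconclusive.

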## Discussion

To the best of our knowledge, the present FATSOMCAN study is the first randomized study to assess the effects of an exercise program, combining high and moderate intensities, on insomnia and other side effects in breast cancer patients during chemotherapy and after a follow up of 3 months post-exercise intervention. Although it has been shown that exercise leads to several positive outcomes in oncology, it remains unknown to date whether exercise is a valuable option for improving sleep, which is frequently disturbed in cancer patients.

The severity and frequency of insomnia in the breast cancer population deserve special attention in terms of diagnosis, and effective and appropriate management. The importance of treatment stems from the knowledge that insomnia results in more severe fatigue, leads to mood disturbances, contributes to immunosuppression, alters quality of life, and potentially affects the course of the cancer [36–38]. Insomnia in cancer may be due to several causes, which can persist over time. Accordingly, the 3P behavioral model, also known as the Spielman Model [39], delineates how insomnia occurs acutely, but how acute insomnia becomes chronic and self-perpetuating. Savard and Morin [40] distinguished between three types of factors that can influence insomnia: enduring factors that predispose an individual for sleep problems, acute factors that precipitate the onset of sleep problems, and factors that perpetuate the maintenance of sleep problems. Savard et al. [41] further showed that the prevalence rate of the combined insomnia syndrome and symptoms was 69.6% at the time of diagnosis and 59.6% at 2 months after, with higher values for breast cancer. Sleep disturbances need to be thought of as part of the symptom cluster often associated with breast cancer. The concept of symptom clusters, including poor sleep/insomnia, fatigue, psychological distress, depression, and pain, has been described in several studies. The more symptoms within the symptom cluster the patients experience before the start of chemotherapy, the worse the symptoms they experience during chemotherapy [42–44]. Gherman et al. [45], who examined insomnia in the context of breast cancer, reported that approximately 50% of insomnia severity was related to the symptom cluster, with the rest being unique to insomnia. Nevertheless, it has been repeatedly reported in literature that insomnia is strongly correlated with fatigue in breast cancer survivors [46–48]. Schultz et al. [49] suggested that focusing on sleeping problems might be beneficial for fatigue symptoms in those women. The current study might reveal more insights into the importance of a good sleep on multiple symptoms in breast cancer patients.

Among available treatment options for insomnia, hypnotic medications are the most commonly used. Nevertheless, some drawbacks of these medications include their adverse side effects, risk of tolerance, dependence and insomnia rebound. In addition, in the context of breast cancer, there is potential reluctance by patients to take additional medications.

Furthermore, there is a growing body of evidence about the effectiveness of CBT for insomnia (CBT-I). Its efficacy has been demonstrated in the specific context of cancer [50, 51]. Its benefits are comparable to, or better than those observed with pharmacotherapy, in patients with insomnia [52, 53].

Over the past few years, research evidence has highlighted the benefits of physical exercise in reducing side effects in patients undergoing chemotherapy and have reported an improvement in physical functioning, cardiac function, body composition, bone density, cognitive function, fatigue, psychological disorders, immune function and quality of life [54–56]. Conversely, to the best of our knowledge, very few studies have investigated the effects of an exercise program on insomnia in breast cancer. Kreutz et al. [57] showed that physical activity (i.e., walking, aerobic exercise, resistance exercise or a combination of both) tended to outperform mind-body exercise (i.e., yoga, Tai Chi and Qigong) during treatment, with significant effects on subjective sleep outcomes. Mercier et al. [13] reported, in their meta-analysis, the need to assess the effect of physical exercise on sleep disturbances to confirm the available empirical evidence and to determine to what extent exercise is beneficial as a sleep enhancing intervention in cancer patients. Indeed, due to the heterogeneity of studies (varying small sizes, samples of mixed cancer diagnoses, different types or doses of exercise, exercise supervised or not), no consensus exists regarding the optimal exercise prescription against insomnia.

The FATSOMCAN study has several strengths including: (1) a multicenter randomized controlled design using clinical level of insomnia at baseline as an inclusion criterion, (2) a large sample size, (3) evaluation of sleep as the main outcome, (4) objective sleep assessments using ambulatory polysomnography and actimeter, (5) follow-up variables to assess the sustainability of therapeutic gains over time.

Furthermore, we propose a supervised endurance training program that alternates moderate and high intensities, with personalized target intensities, adjusted according to the physical characteristics of the subject. This type of training has already been proposed to patients presenting cardiovascular disease or metabolic syndrome [58–61], with a growing body of evidence emerging in cancer patients [16]. Training has been associated with many benefits, such as improving physical functioning and fitness (i.e., V˙O_2_ peak), reducing side effects of cancer treatments, preventing bone loss and weight gain, increasing muscle strength, decreasing cancer-related fatigue and improving quality of life [16, 62–66].

While exercise is safe and well tolerated by patients undergoing cancer treatments or in the rehabilitation phase [67], findings also show that knowing, and managing insomnia with physical activity offers interesting therapeutic prospects for cancer treatment. However, most studies use only questionnaires without recording objective sleep using polysomnography [57, 68].

This clinical trial will provide additional evidence regarding the effectiveness of physical exercise during chemotherapy in minimizing insomnia, improving sleep quality, reducing fatigue, pain, anxiety, increasing cardio-respiratory fitness and health-related quality of life. If shown to be effective, exercise intervention programs could be welcome addition to the standard program of care offered to patients with breast cancer.

